### Treatment regimen

#### Treatment frequency and duration

Women allocated to the acupuncture group will receive a total of 11 treatments of acupuncture over 12 weeks (twice a week for the first two weeks, weekly for four weeks, then fortnightly for 3 treatments). This tapering schedule is consistent with usual clinical practice. Needles are retained for 30 minutes.

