#### Dealing with missed sessions

At the time of enrolment, participants are to be made aware of the nature of their commitment over the twelve week treatment period and encouraged to notify the research office, [name] or the treating practitioner as soon as a break in treatment is foreseen. If treatments are missed, all attempts will be made to complete ten treatments within the eight weeks, providing there is at least a 2 day interval between treatments A break in the intervention schedule may be unavoidable, due to illness or holiday. If the acupuncturist becomes aware that a break of more than two weeks is likely, they will be instructed to liaise with [name] for advice on how to deal with this. [name] or the research assistant will liaise with the participant to determine the cause of missed sessions and will attempt as much as possible to implement appropriate measures to minimise further breaks in between treatments.

As analysis will be by intention-to-treat (that is, all data will be analysed even if a participant has dropped out from the trial), a minimum number of treatment sessions to meet the protocol has not been specified.

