### Treatment regimen

#### Treatment frequency and duration

Women allocated to the AEA group will receive a total of 6 treatments of acupuncture over 12 weeks (twice a week for the first two weeks, then fortnightly for four treatments).

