#### Dealing with missed sessions

At the time of enrolment, participants are to be made aware of the nature of their commitment over the twelve week treatment period and encouraged to notify the research office, [name] or the treating practitioner as soon as a break in treatment is foreseen. If treatments are missed, all attempts will be made to complete ten treatments within the eight weeks, providing there is at least a 2 day interval between treatments A break in the intervention schedule may be unavoidable, due to illness or holiday. If the acupuncturist becomes aware that a break of more than two weeks is likely, they will be instructed to liaise with [name] for advice on how to deal with this. [name] or the research assistant will liaise with the participant to determine the cause of missed sessions and will attempt as much as possible to implement appropriate measures to minimise further breaks in between treatments.

As analysis will be by intention-to-treat (that is, all data will be analysed even if a participant has dropped out from the trial), a minimum number of treatment sessions to meet the protocol has not been specified.

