#### Pre-intervention/ Baseline visit

The purpose of the baseline visit is to obtain informed consent, collect baseline and demographic measures, randomise the participant, and organise the acupuncture treatments for the participant.

*Informed consent*

If the research assistant is not a practising acupuncturist, the participant will be telephoned by [name], an acupuncturist and researcher, in order to provide details about the acupuncture treatment and answer any queries about acupuncture. This is essential so that the participant can provide informed consent after understanding the risks and benefits of acupuncture treatment. This telephone call will take place prior to the baseline clinic visit.

During the clinic visit, which will take place at the National Institute of Complementary medicine, Campbelltown Campus, Western Sydney University, the participant will meet with the research assistant to provide informed consent.

*Baseline and demographic/medical measures*

The participant will have baseline outcome measures taken as per the following section on Data Collection. Briefly they include:

- Anthropometric measures and blood pressure
- Surveys on quality of life, anxiety and depression, weight self-efficacy, and internal locus of control.
- Measures of insulin resistance by blood tests collected by Laverty Pathology
- Testosterone, Free testosterone and Free Androgen Index collected by Laverty Pathology
- Clinical Hyperandrogenism as assessed by the Ferriman Gallwey score
- Heart rate using ECG monitoring at Headbox laboratory on the WSU Campbelltown Campus and also using a hand-held ambulatory monitor at the same time

Participants will also provide demographic and medical history details.

*Randomisation*

Participants will be assigned a randomisation ID number.

*Acupuncture treatments*

Participants are provided with information about the acupuncture treatments, will choose a treating acupuncturist for the intervention, and the research assistant will organise the participants’ acupuncture treatments according to the schedule.

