# Data Collection

Data on recruitment, retention, adherence and acceptability rates will be entered into Redcap clinical trial management software. These are defined as:

1. Recruitment rates (number of enquiries and number of enrolments per month of active recruitment; percentage conversion to enrolment measured as n enrolled/n of enquiries, and n enrolled/n potentially eligible);
2. Retention rate (n completing 12 week intervention and outcome measures/n enrolled)
3. Adherence rates (n completing at least 8 of 11 acupuncture treatments and 4 of 6 Neurova treatments; n of hours of wear of the Neurova^TM^ device/percentage of women who wore the device for the prescribed 96 hr duration; n completing all recommended phone calls with the GHS);
4. Acceptability is measured using an exit survey which includes questions on perceived benefits of body acupuncture, AEA, and health coaching, perceived detriments of being in the trial, likelihood of recommending the study to family or friends measured on a 5 point Likert scale ranging from “I would definitely participate/recommend it” to “I would definitely not participate/recommend it”;

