## Proposed Analyses

Recruitment, retention and adherence rates are presented with descriptive statistics. Mixed model ANOVAs will be used to determine within-group differences for continuous outcomes between baseline and 3 months, and ANCOVAs for between-group differences for continuous outcomes with baseline score as a co-variate. Intention-to-treat analysis will be used.

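### The AEA schedule gives a total of 6 treatments but a pattern of 8, so the adherence threshold of 4 of 6 has no clear denominator; the missed-session rule of ten in eight weeks fits neither active arm

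*Protocol*

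**What the plan says.** **AEA regimen (Protocol 6.2.3, Treatment frequency and duration).** Women receive "a total of 6 treatments of acupuncture over 12 weeks (twice a week for the first two weeks, then fortnightly for four treatments".

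**Adherence (Protocol 8, Data Collection).** The AEA criterion is at least "4 of 6 Neurova treatments"; the body-acupuncture criterion is at least 8 of 11. Hours of device wear are reported as well. Section 2.2.1 makes adherence part of the primary endpoint, and section 9.2 says how it is analysed: "Recruitment, retention and adherence rates are presented with descriptive statistics".

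**Body-acupuncture regimen (Protocol 6.1.3).** A total of 11 over 12 weeks, given as "twice a week for the first two weeks, weekly for four weeks, then fortnightly for 3 treatments".

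**Missed sessions.** For AEA (6.2.3), staff try to "complete ten treatments within the eight weeks, providing there is at least a 2 day interval between treatments". The body-acupuncture rule (6.1.3) uses the same words: "all attempts will be made to complete ten treatments within the eight weeks".

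**Booking (Protocol 7.1.1, baseline visit).** The research assistant arranges each woman's "acupuncture treatments according to the schedule".

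**The concern.** The AEA total and the AEA pattern stand in one sentence and disagree. Staff who book from the total and staff who book from the pattern would deliver different courses, in an arm that section 6.2.1 describes as a fixed protocol and that is treated in several private clinics.

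The adherence criterion inherits the problem. It is written against 6, so its meaning depends on which course was delivered. This study exists to show whether a larger trial can be run, and an AEA adherence rate with an uncertain denominator is a weak input to that decision.

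The missed-session rule is a second, independent fault. It asks for more AEA treatments than the course contains on either count, within a period that is not the treatment period.

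**Working it through.** **1. Count the sessions.** Inputs are the schedules in 6.1.3, 6.2.3 and the Study Synopsis. The two schedules that add up show how the document counts.

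| Schedule | Stated total | Count from the pattern |
|---|---|---|
| Body acupuncture, 6.1.3 | 11 | 2 × 2 + 4 + 3 = 11 |
| Synopsis | 12 | 2 × 4 + 8/2 = 12 |
| AEA, 6.2.3 | 6 | 2 × 2 + 4 = **8** |

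The body-acupuncture sentence opens with the same phrase as the AEA sentence and reaches 11 only if that phrase means four sessions. (The Synopsis total of 12 differs from the 11 in 6.1.3; it is used here only to check the counting.)

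No literal reading of the AEA pattern gives 6. Six requires changed words: one session a week for two weeks plus four fortnightly (2 + 4), or twice weekly for two weeks plus two fortnightly (4 + 2).

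**2. What the threshold means.**

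- 4 of 6 = 66.7%
- 4 of 8 = 50.0%
- 6 of 8 = 75.0%
- Body acupuncture, 8 of 11 = 72.7%

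Under the 8-session pattern the first two weeks supply 2 × 2 = 4 treatments, so the threshold is met with all four fortnightly sessions missed. With 6 sessions and a weekly start, the first two weeks supply 2, so at least 4 − 2 = 2 fortnightly sessions are needed.

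**3. How far the rate could move (illustration).** Assume each session is attended independently with the same probability. That probability is not in the documents, so a range is shown.

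| Attendance per session | P(at least 4 of 6) | P(at least 4 of 8) |
|---|---|---|
| 0.6 | 0.54 | 0.83 |
| 0.7 | 0.74 | 0.94 |
| 0.8 | 0.90 | 0.99 |

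The same attendance behaviour gives clearly different adherence rates.

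**4. Dose.** With 13 women randomised to AEA, full delivery is 13 × 6 = 78 or 13 × 8 = 104 treatments. Maximum wear per woman is 6 × 96 = 576 h or 8 × 96 = 768 h.

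**5. Missed-session rule.** The target of ten exceeds the whole AEA course by 10 − 6 = 4 or 10 − 8 = 2. For body acupuncture it is 11 − 10 = 1 short of the course. Eight weeks is 4 short of the 12-week period in both arms, and the paragraph containing the rule itself refers to twelve weeks.

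**The case against.** **The adherence definition is consistent with the stated total.** Six appears in both 6.2.3 and section 8. The 50% reading arises only if clinics follow the pattern while the analysis keeps 4 of 6. This stands, and it is why the effect on the threshold is conditional. It does not remove the contradiction in the sentence from which sessions are booked.

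**The damage can be repaired afterwards.** Each treatment goes on a case report form, wear hours are reported separately, and any threshold can be recomputed. Adherence is descriptive, the protocol attaches no progression cut-off to it, and the analysis is by intention to treat with no minimum number of sessions. All of this stands and limits the harm. A dose that differed between women could not be repaired at analysis.

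**The arms need not share a threshold.** Correct: the protocol never says they should, and 73% against 67% is already unequal. The body-acupuncture figure is context only.

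**Stronger readings that a reader might infer, and that the documents do not support:**

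- *Two sessions a week cannot be worn in full, so the pattern must be the error.* Section 8 does speak of the "percentage of women who wore the device for the prescribed 96 hr duration", and 2 × 96 = 192 h exceeds a 168 h week. But the second wear may run into the next week. Insertions on days 0, 4, 8 and 12 fall two per week and allow four full wears without overlap. Section 6.2.2 also makes 96 hours an upper limit. There is no proven conflict and no need for a new minimum interval.
- *The two counts differ by a known number of devices.* The needles are described as disposable, but the protocol does not say that the device is single-use. Only treatments can be counted.
- *The AEA missed-session rule was copied from body acupuncture.* The wording is identical, but that does not show the direction, and the rule fits neither arm.

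**Conclusion.** The concern holds. The AEA total of 6 and the AEA pattern of 8 cannot both be right. The documents do not establish which is wrong; 6 is likelier because section 8 repeats it.

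If 8 sessions are booked and the threshold is left at 4, AEA adherence is judged at 50% of the course instead of 67% and can be earned in the first two weeks. The consequence is an unclear delivered dose and an unclear descriptive rate within the primary endpoint.

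The missed-session rule is wrong for both active arms whichever AEA count is chosen.

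The session count and the percentages need no assumption beyond reading the opening phrase as 6.1.3 does. The attendance figures are illustrative. Any calendar week given to a fortnightly session is also assumed, because the protocol does not say when the first one falls: with a weekly start, the fourth of six sessions comes in week 6 if the first fortnightly session is in week 4, or in week 5 if it is in week 3.

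**What to change.** 1. **Section 6.2.3, frequency.** Make the total and the pattern agree. If 6 is meant, for example: *weekly for two weeks, then every two weeks for four treatments*. Keeping the twice-weekly start with only two fortnightly sessions also gives 6, but then 4 of 6 could still be reached in the first two weeks and treatment would end sooner.
2. **Section 8, adherence.** If 6 is confirmed, leave 4 of 6. If 8 is chosen, use 6 of 8. It is the smallest count that reaches two-thirds of the course (8 × 2/3 = 5.3, rounded up), and it requires at least two fortnightly sessions. At 75% it is somewhat stricter than 4 of 6.
3. **Missed sessions, 6.2.3 and 6.1.3.** Replace the ten-in-eight-weeks target with each arm's own total over 12 weeks: the chosen AEA count, and 11 for body acupuncture.

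The cost is a short wording amendment, submitted for ethics approval in the usual way. It adds no participants, visits or assessments, apart from the two extra AEA sessions per woman if 8 is chosen over 6. If women have already been treated, report how many AEA sessions each was scheduled to receive beside the adherence rate.

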#### Dealing with missed sessions

At the time of enrolment, participants are to be made aware of the nature of their commitment over the twelve week treatment period and encouraged to notify the research office, [name] or the treating practitioner as soon as a break in treatment is foreseen. If treatments are missed, all attempts will be made to complete ten treatments within the eight weeks, providing there is at least a 2 day interval between treatments A break in the intervention schedule may be unavoidable, due to illness or holiday. If the acupuncturist becomes aware that a break of more than two weeks is likely, they will be instructed to liaise with [name] for advice on how to deal with this. [name] or the research assistant will liaise with the participant to determine the cause of missed sessions and will attempt as much as possible to implement appropriate measures to minimise further breaks in between treatments.

As analysis will be by intention-to-treat (that is, all data will be analysed even if a participant has dropped out from the trial), a minimum number of treatment sessions to meet the protocol has not been specified.

### Other components of treatment

No additional Chinese medicine treatments will be provided including body acupuncture, Chinese herbal medicine, or additional physical or stimulation treatments such as moxibustion or cupping.

Participants will attend for treatment at private clinics of the treating acupuncturists**.** Practitioners are trained to ask about adverse events, and to treat patients warmly and courteously. All efforts will be made to ensure the participants have a comfortable acupuncture experience.

Practitioners will record details of each treatment on an individual Case Report Form which will be kept in a locked cupboard in the clinic and returned to the research team at the end of the study.

### Quality assurance

As part of monitoring of treatment fidelity and quality assurance, practitioners are requested to take a digital photo of the first insertion of the Neurova that they perform, to be verified by the Chief Investigator and by NESI Corp (the manufacturers). This photo will not contain any identifying features such as facial features. The photo will be labelled with the participant ID number and date of treatment only, and emailed to [name], who will then store the photograph on a secure University cloud-based server.

### Practitioner background

A minimum of six practitioners have been chosen to administer the treatments. They are have a Bachelor degree in Chinese Medicine, have five or more years of clinical experience and are registered with the Chinese Medicine Registration Board.

Practitioners will receive training from [name], an experienced acupuncture researcher. Training will take place 4-6 weeks prior to anticipated start of recruitment. They will receive a detailed Practitioner Training Manual. Training will be “hands on”. Refresher training will be provided if there has been a break of two months or more in between administering the trial interventions to participants.

Participants are free to choose which practitioner they wish to see according to convenience (location, availability etc) however they are to be aware that there may be a “waitlist” for particular practitioners. Practitioners may also notify the research assistant or [name] when they are unable to take on new participants temporarily due to other commitments.

## Control intervention

The control intervention is lifestyle intervention only (see 6.4.1below).

## Co-interventions

Although participants will be encouraged to avoid using new co-interventions, co-interventions including complementary therapies will be allowed.

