**Study Synopsis**

| **Title:** | **Acupuncture or auricular electro-acupuncture as adjuncts to lifestyle interventions for weight management in PCOS: a randomised controlled feasibility study** |
| --- | --- |
| **Sponsor:** | **NHMRC CRE in PCOS (Project Grant)** |
| **Protocol Number:** | **V12** |
| Development Phase: | Phase II |
| Indication: |  |
| **Objectives of the Study:**  Primary Objective: | Determine feasibility and acceptability of study procedures |
| Secondary Objective(s): | Determine an effect size for acupuncture and lifestyle vs AEA and lifesyle vs lifestyle alone and examine for a trend between groups for change in body weight, BMI, Heart Rate Variability and insulin sensitivity |
| **Study Drugs/Therapeutic Intervention:** | Acupuncture and telephone-based lifestyle intervention compared to AEA and telephone-based lifestyle intervention compared to telephone-based lifestyle intervention alone |
| **Study Design**: | Randomised controlled feasibility study |
| **Study Endpoints** (primary and secondary) | Primary: Recruitment, retention, adherence, acceptability , credibility and safety over the recruitment and intervention periods.  Secondary: Difference between groups for anthropometric measures, blood pressure, health-related quality of life, menstrual cycles, psychological measures, self-efficacy and locus of control, heart rate variability, insulin, glucose, Sex Hormone Binding Globulin, total and free testosterone and free androgen index |
| **Sample size** (by treatment group):  Sample Size Determination: (If applicable) | We aim to analyse 30 women (10 in each group) at the end of treatment |
| **Total Number of Study Centres** | 1 |
| **Study Duration:** | 12 weeks |
| **Inclusion Criteria:** | - women aged 18-45 years - physician diagnosis of PCOS according to the 2003 Rotterdam Criteria in previous 5 years[14]; - BMI≥25 kg/m^2^; no other endocrine disorders; - not pregnant/no pregnancies in preceding 6 weeks and more than 6 weeks postpartum; - not on the following medications in the 3 months preceding enrolment: metformin or other medications affecting insulin and glucose metabolism, hormonal treatments for PCOS/ART including gonadotrophins and the Oral Contraceptive Pill, pharmaceutical or complementary therapies for weight loss |

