**The potential role of acupuncture**

In non-PCOS populations, acupuncture is more efficacious than sham for weight loss, with mean differences in body weight and Body Mass Index(BMI) of 1.58kg[4] to 4.4kg[5], and 0.6 kg/m^2^[4]to 2.79 kg/m^2^[6] respectively (3.5-5% decrease from baseline)[4-7]. These effects are mediated through alterations in obesity-related peptides, appetite regulation, insulin levels, free fatty acids and inflammatory markers[8] and are sustained after end-of-treatment[5]. RCTs conducted in China indicate that acupuncture + metformin is superior to metformin alone in women with PCOS for reducing BMI[9]. The overall effect size is unclear, although one study reported a mean difference of 0.97kg/m^2^ (95% CI 1.51, 0.43) for acupuncture + metformin compared to metformin alone[10].

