### Inclusion Criteria

- women aged 18-45years;
- physician diagnosis of PCOS according to the 2003 Rotterdam Criteria in previous 5 years [14];
- BMI≥25 kg/^2^; no other endocrine disorders;
- not pregnant/no pregnancies in preceding 6 weeks and more than 6 weeks postpartum;
- not on the following medications in the 3 months preceding enrolment: metformin or other medications affecting insulin and glucose metabolism, hormonal treatments for PCOS/ART including gonadotrophins and the Oral Contraceptive Pill, pharmaceutical or complementary (nutritional/herbal) treatments for weight loss

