### Exclusion Criteria

- Planning to conceive within the next 3 months
- Needle acupuncture in the previous 3 weeks
- Unable to provide informed consent.
- BMI >40
- anticoagulant use
- pacemaker use
- immunocompromise
- valvular heart disease
- Currently breastfeeding, or breastfeeding within the last 6 weeks

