### Other components of treatment

Treating acupuncturists may provide diet and lifestyle advice according to Chinese medicine principles. This advice usually consists of advice to avoid ingesting foods that are considered too “hot” or “cold” for the patient’s constitution. However, no additional Chinese medicine treatments will be provided including Chinese herbal medicine, or additional physical or stimulation treatments such as moxibustion or cupping.

Participants will attend for treatment at private clinics of the treating acupuncturists. Treating acupuncturists are advised that they may proceed according to usual clinical practice with the following limitations:

- The acupuncture protocol must be targeted at weight loss as the primary outcome
- The acupuncture protocol must adhere to the standardization applied to acupuncture points, manipulation, stimulation, retention time, frequency as described above
- Only body acupuncture, diet and lifestyle advice (according to Chinese medicine) may be provided.

Practitioners are free to practise as they usually practise. They will be trained to ask about adverse events, and to treat patients warmly and courteously. All efforts will be made to ensure the participants have a comfortable acupuncture experience.

Practitioners will record details of each treatment on an individual Case Report Form which will be kept in a locked cupboard in the clinic and returned to the research team at the end of the study.

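### Section 6.4 allows complementary therapies in every arm without excepting acupuncture, so unrecorded outside acupuncture among lifestyle-alone women can dilute the secondary effect sizes

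*Protocol*

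**What the plan says.** Protocol Section 6.3 reads: "The control intervention is lifestyle intervention only (see 6.4.1below". Section 6.4, which follows it, reads: "Although participants will be encouraged to avoid using new co-interventions, co-interventions including complementary therapies will be allowed". It names no arm and makes no exception for the treatments under test.

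Two sections limit what is given as trial treatment. For body acupuncture (Section 6.1.4): "Only body acupuncture, diet and lifestyle advice (according to Chinese medicine) may be provided". For AEA (Section 6.2.4): "No additional Chinese medicine treatments will be provided including body acupuncture, Chinese herbal medicine".

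On recording, Appendix 1 lists concomitant medications at Visits 1 and 2 and has no line for outside acupuncture. Section 10.2 asks about new medicines and changed medication. The adherence definitions in Section 8 cover trial acupuncture sessions, device wear and coaching calls, but not acupuncture received by controls.

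Secondary objective 2 (Section 2.1.2) is an effect size for acupuncture plus lifestyle against lifestyle alone, and the synopsis adds AEA. Section 9.2 specifies intention-to-treat, with ANCOVA adjusting for baseline.

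On acupuncture before entry, the synopsis and Section 4.1.2 both exclude "Needle acupuncture in the previous 3 weeks". Separately, a 3-month item covers "pharmaceutical or complementary therapies for weight loss" in the synopsis and "pharmaceutical or complementary (nutritional/herbal) treatments for weight loss" in Section 4.1.1.

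**The concern.** The trial is open-label. Women hear about acupuncture before giving written consent, and the Background reports that the team's qualitative work found it highly acceptable. One third of the women are then allocated to none. Some controls may seek it elsewhere, and Section 6.4 does not make that a deviation.

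The study is meant to inform a fully powered trial. Controls who receive the test treatment narrow the intention-to-treat contrast, and a later trial planned on the narrowed figure would be larger than it need be. How often controls obtain acupuncture is also something a feasibility study should learn, and this protocol plans no way of learning it.

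**Working it through.** **1. Is outside acupuncture within the permission?** Section 6.4 covers complementary therapies as a class, and acupuncture is one. Sections 6.1.4 and 6.2.4 do not close the gap, because they bind the trial practitioners and not what a woman obtains elsewhere. Section 6.2.4 keeps body acupuncture out of AEA treatment, so the protocol treats the mixture as unwanted there. Section 6.4 leaves it open outside the trial.

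**2. Would it be recorded?** Neither Appendix 1 nor Section 10.2 asks about it. The case report forms are not shown, so the most that can be said is that the protocol does not require it.

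**3. The plan's own figure.** The target is 30 analysed, 10 per arm. At 20% attrition, 10/(1 − 0.20) = 12.5, rounded up to 13; 3 × 13 = 39. At 25%, 30/(1 − 0.25) = 40. The stated 39 is consistent with the stated 20–25% range: losing 9 of 39 is 23.1%. No power, alpha or SD is stated, and crossover does not change 39 or 30.

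**4. Size of the dilution.** Inputs:
- D is the true difference. The Background gives 1.58 to 4.4 kg, against sham in non-PCOS populations, used here only for scale.
- c is the fraction of lifestyle-alone women who obtain acupuncture. The protocol gives none, so a range is assumed.
- e is the share of the trial effect that outside acupuncture delivers. e = 1 is a full crossover.

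Expected intention-to-treat difference = D × (1 − c × e). With e = 1:

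| c (assumed) | D = 1.58 kg | D = 4.4 kg | Later trial's sample size, 1/(1 − c)² |
| --- | --- | --- | --- |
| 10% | 1.42 | 3.96 | × 1.23 |
| 20% | 1.26 | 3.52 | × 1.56 |
| 30% | 1.11 | 3.08 | × 2.04 |
| 40% | 0.95 | 2.64 | × 2.78 |

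With 10 analysed per arm, one full crossover is c = 1/10, or 10% of D. With e below 1 the loss is smaller.

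For AEA against lifestyle, the expected difference is the AEA effect minus c times the effect of the outside acupuncture. The loss is at most the fraction c provided outside acupuncture works no better than AEA, which is an assumption. AEA women who have body acupuncture elsewhere also blur the AEA-versus-acupuncture comparison.

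**5. Comparison with sampling error.** The half-width of the 95% interval at 10 per arm is t(0.975, 18 df) × SD × √(2/10). For an assumed SD of weight change of 3 to 5 kg this is 2.82 to 4.70 kg. One or two full crossovers shift the expected difference by 0.16 to 0.32 kg (D = 1.58) or 0.44 to 0.88 kg (D = 4.4).

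**The case against.** Section 6.4 does not name acupuncture and already discourages new co-interventions. Because needle acupuncture in the 3 weeks before entry excludes a woman, a control who has it during the trial would usually be starting something new. The crossover rate is assumed, and outside acupuncture may not match an 11-session protocol with electrical stimulation. Body acupuncture is delivered semi-pragmatically, and allowing usual co-interventions is defensible in a small open-label feasibility study. The likely shift lies well inside the sampling error.

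Most of this stands, and it limits how serious the point is. It does not remove it. Discouraging is not excluding, and the control arm is defined as lifestyle only. Sampling error is visible in the confidence interval, whereas unrecorded crossover is visible nowhere.

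A reader might go further and infer that a 3-week washout lets carry-over dilute the contrast, since the Background says the effects of acupuncture persist after treatment. The documents do not support that. Acupuncture before entry precedes randomisation, is balanced across arms in expectation and is partly absorbed by the baseline covariate. No duration is given. A fading effect could narrow the contrast or widen it.

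A reader might also see a flat contradiction between a 3-month and a 3-week rule for acupuncture. But the 3-month item closes a list of medications, and the synopsis carries the same 3-week needle-acupuncture exclusion as Section 4.1.2. The difference between the synopsis and Section 4.1.1 is an ambiguity of wording.

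**Conclusion.** The point holds for crossover after randomisation. The protocol permits lifestyle-alone women to receive the test treatment outside the trial and does not require it to be recorded. Under intention-to-treat this can pull the two comparisons with lifestyle alone towards zero, by up to the fraction c: about 10% per full crossover at 10 analysed per arm. Whether it will happen, and how often, cannot be said, because no rate is given. The size rests on full effect in those who cross over and, for AEA, on outside acupuncture working no better than AEA.

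The consequence is confined to a secondary objective. The feasibility endpoints and the sample size stand. The change is still worth making, because it is cheap and the effect size is meant for planning the next trial.

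**What to change.** - **Sections 6.3 and 6.4:** reconcile them so that body or ear acupuncture obtained outside the trial is excepted, in every arm, from the general permission for co-interventions.
- **Appendix 1:** add a question on outside acupuncture (type, dates, number of sessions) at Visits 1 and 2.
- **Sections 8 and 9.2:** keep crossovers in their randomised arm and report the number per arm beside the effect size, as a feasibility result.
- **Eligibility:** align the synopsis with Sections 4.1.1 and 4.1.2, so that it is clear which item governs prior acupuncture. The length of the washout is for the investigators to settle.

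The cost is a few sentences in the protocol and one question at two visits that already take place. Controls who want acupuncture are asked to wait until Visit 2, at week 12.
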